### Pilot study

A pilot study has already been conducted. We enrolled 10 knees with primary osteoarthritis undergoing. Five knees were operated with a tourniquet, and the other 5 knees were operated without a tourniquet. Postoperative swelling, VAS score, quadriceps morphology, and function were recorded. Finally, the pilot study found that there was no significant difference in these outcomes between the two sides, indicating that a tourniquet might not cause severe quadriceps injury.

### Sample size estimation

The primary hypothesis of this trial based on our previous pilot study is that quadriceps thickness in the tourniquet group is not less than that in the non-tourniquet group. The risk of class I error of the hypothesis is controlled within 5% during sample size estimation (*α* = 0.05).

Quadriceps thickness is 3.1 ± 0.5 cm in the non-tourniquet group and 3.1 ± 0.6 cm in the tourniquet group. Non-inferiority margin (*σ*) is 0.31, which is 10% of the average quadriceps thickness in the non-tourniquet group, *α* = 0.025 (unilateral), *β* = 0.2. We apply the non-inferiority test by PASS14 and find that we need at least 51 participants in each group. We determine that a total of 51 participants per group would have an 80% statistical power in detecting a tourniquet impact between the two groups. This will result in a total of 102 participants. Estimating that 30% of participants would drop out, a sample size of 130 participants is considered to be adequate for this study.

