**Fig. 1 Fig1:**
[figure not shown]
Flowchart of the study process

We assume the primary hypothesis of this trial is that quadriceps thickness in the tourniquet group is not less than that in the non-tourniquet group (non-inferiority study).

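### The stated 80% power to detect a tourniquet impact is really 80% power to exclude a 0.31 cm loss when the true difference is zero

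*Protocol article*

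**What the plan says.** The text under Fig. 1 and the opening of Sample size estimation both set the primary hypothesis as non-inferiority of the tourniquet group on quadriceps thickness. The sizing inputs follow that hypothesis:

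- Means and SDs: "Quadriceps thickness is 3.1 ± 0.5 cm in the non-tourniquet group and 3.1 ± 0.6 cm in the tourniquet group".
- Margin: it "is 0.31, which is 10% of the average quadriceps thickness in the non-tourniquet group".
- Error rates: alpha 0.025 one-sided and beta 0.2.
- Result: "We apply the non-inferiority test by PASS14 and find that we need at least 51 participants in each group".

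The next sentence describes what this achieves: "a total of 51 participants per group would have an 80% statistical power in detecting a tourniquet impact between the two groups". It gives no size of impact.

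Statistical analysis compares the primary outcome with a Mann-Whitney U test. Significance is two-sided at 0.05, apart from a Bonferroni correction. The section also plans bootstrap 95% confidence intervals for the between-group difference of medians. It does not mention the margin.

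**The concern.** Concluding non-inferiority and detecting an impact are opposite conclusions. Under the stated inputs the true impact is zero, so there is nothing to detect, and the 80% cannot be the probability of detecting it. The sentence attaches the power of one test to the conclusion of another.

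This matters because of how the two sections combine. The power sentence claims 80% for detecting an unspecified impact, and the analysis section tests for a difference, two-sided, without using the margin. A reader of the final report could take a non-significant thickness result as absence of a tourniquet impact, backed by 80% power. The design does not support that for losses smaller than the margin. The trial's actual question, whether a loss of 0.31 cm or more can be excluded, could go without an explicit answer.

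**Working it through.** **Inputs** (Sample size estimation): SDs 0.5 and 0.6 cm, true difference 0, margin 0.31 cm, one-sided alpha 0.025, power 80%, 1:1 allocation.

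**1. Reproduce the 51.** The normal approximation gives

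n per group = (0.5² + 0.6²) × (1.960 + 0.842)² / 0.31² = 0.61 × 7.849 / 0.0961 = 49.8, so 50.

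The unequal-variance t version (noncentral t) gives 79.3% at n = 50 and 80.1% at n = 51. The smallest n reaching 80% is therefore 51, as stated. A one-sided alpha of 0.05 would give 40 by the normal approximation, so 0.025 is the level that was used.

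**2. What the 80% refers to.** At n = 51 the standard error is √(0.61/51) = 0.1094 cm. The noncentrality is (0.31 − true loss)/0.1094, which is 2.83 at zero loss. The 80.1% is the probability that the lower confidence limit excludes a loss of 0.31 cm when there is no loss.

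**3. Both kinds of power at 51 evaluable per arm.** Non-inferiority power uses (0.31 − loss)/0.1094 at one-sided 0.025. Detection power uses loss/0.1094 at two-sided 0.05. The losses between 0 and 0.31 cm are illustrative; the protocol names none of them.

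| True loss (cm) | Power to conclude non-inferiority | Power to detect a difference |
|---|---|---|
| 0 | 80% | none to detect |
| 0.05 | 65% | 7% |
| 0.10 | 48% | 15% |
| 0.20 | 17% | 44% |
| 0.31 (margin) | 2.5% (the alpha level) | 80% |

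**4. Where the sentence would be true.** The difference detectable with 80% power at 51 per arm is (1.960 + 0.842) × 0.1094 = 0.306 cm by the normal approximation, which is practically the margin. The agreement is algebraic: the distance from margin to zero equals the difference to be detected, and the variance and critical value are the same.

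**5. Dependence on the evaluable number.** The trial enrols 65 per group, and 51 is the evaluable target. At 65 per arm with no loss, non-inferiority power is 89% at zero difference, and detection power is 18% at 0.10 cm and 54% at 0.20 cm. At about 45 per arm (130 × 0.70 = 91 in total, using the protocol's 30% dropout) the same figures are 75%, 14% and 40%. The pattern does not change.

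All these figures are for a t-type comparison of means. For the planned rank test under normal data, multiplying n by 3/π gives detection power of about 79% instead of 81% at 0.31 cm (both by the normal approximation), which is a negligible change.

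**The case against.** The best defence is that nothing is hidden. The test, margin, one-sided alpha, beta and equal means all stand just before the disputed sentence, so a careful reader can recover what the 80% means. Assuming zero true difference is a common convention for non-inferiority, and 51 is right. The sentence is even numerically true if the impact is read as 0.31 cm. The analysis section also plans 95% confidence intervals, which could be set against the margin. All of this stands, and it limits the point to a misdescribed design property. It does not remove it, because the sentence never states the 0.31 cm condition and the analysis section never links the intervals to the margin.

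Two stronger readings are tempting, and the documents do not support them.

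- **That assuming no impact makes the trial miss a 5% loss (0.155 cm) about 7 times in 10.** The 71% is correct arithmetic for 51 evaluable per arm (64% at 65, 74% at 45), but it does not follow from the equal-means assumption. An ordinary difference calculation for 0.31 cm gives the same n and the same 29% power at 0.155 cm. No section names 5% as a target. It lies inside the 10% margin that the design tolerates, so missing it is no failure of the non-inferiority objective.
- **That the pilot makes the zero-difference assumption untenable.** The Pilot study section says "there was no significant difference in these outcomes between the two sides, indicating that a tourniquet might not cause severe quadriceps injury", which is hedged. An interval for five against five knees would need assumed SDs and independent groups. The protocol does not say that its SDs come from the pilot, and its reference to two sides leaves paired knees possible.

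Nor do the documents say that a non-significant result will be reported as no impact. That is a risk of misreading, not a stated plan.

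**Conclusion.** The point holds as a misstatement of what the sample size delivers. The 80% is power to conclude non-inferiority at a 0.31 cm margin, one-sided 0.025, if the true difference is zero. As detection power it applies only to a difference of about 0.31 cm and is well below 80% for smaller losses. Non-inferiority power itself drops quickly with a small true loss. These values rest on the protocol's SDs, 51 evaluable per arm and a comparison of means.

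The sample size calculation is not in error. The misstatement is more than cosmetic because the planned primary test is a two-sided difference test that does not use the margin. The point is worth correcting before analysis, since it governs what a non-significant result may be taken to show.

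**What to change.** 1. In Sample size estimation, replace the sentence with: *51 evaluable per group give 80% power to conclude non-inferiority at a 0.31 cm margin (one-sided 0.025) if the true difference is zero.* Optionally add that this power is 65% for a true loss of 0.05 cm and 48% for 0.10 cm.
2. In Statistical analysis, state that the primary conclusion rests on comparing the 95% confidence interval of the between-group thickness difference with the 0.31 cm margin. Name the interval used: the margin was set on mean thickness, while the planned bootstrap interval is for medians.
3. In the same section, state that a two-sided p of 0.05 or more will not be reported as absence of a tourniquet impact.

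The cost is a few sentences and a less favourable power statement. No more patients, visits or data are needed, and the Pilot study section can stay as it is.

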### Statistical analysis

The statistician who conducted the analysis is blinded to the group allocation. Summary statistics are used to describe the participant characteristics of the trial groups at baseline in the intention-to-treat (ITT) analysis set. The missing data of quadriceps thickness and stiffness is imputed by the multiple imputation method. The results of multiple imputation data are used as a type of sensitivity analysis for comparing primary outcomes between the groups.

For primary outcomes comparison, the ITT analysis is performed to evaluate the differences between the groups, and effective analysis population (EAP) and per-protocol (PP) analyses are also performed for sensitivity assessment. The primary outcomes do not follow the Gaussian distribution and are presented as median (IQR) and tested by the Mann-Whitney *U* test. Bonferroni correction is used to reduce the significance level. The means (95% CIs) of the between-group differences of the medians are calculated by the bootstrap method (1000 replications). The generalized linear mixed models (GLMM) are also performed for the primary endpoint, including group, gender, age, height, and weight as fixed covariates.

For comparing the secondary and exploratory endpoints, continuous data are presented as means (SDs) or medians (IQRs) as appropriate. The secondary endpoints are analyzed by the linear mixed model (LMM), adjusted for gender, age, height, weight, and other covariates. The correlation type of different measurement time points is assumed as the first-order autocorrelation in the LMM. Exploratory endpoints are compared by the Mann-Whitney *U* test, and the significance level is submitted to Bonferroni correction.

For safety endpoints, categorical data are presented as counts and percentages and tested by the Pearson’s chi-square test or Fisher’s exact test. The 95% CIs of absolute risk differences between the groups are calculated by the Newcombe-Wilson Score method. All statistical analyses are conducted with the statistical package SPSS, V.18.0 (SPSS Inc.) and the R 3.4.0 software. Besides Bonferroni correction, statistical significance is defined as *p* < 0.05with two-sided testing.

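### At 130 enrolled, the sample size section's 30% dropout and 80% power cannot both hold, and an unspecified Bonferroni reduction of the primary significance level was not part of the calculation

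*Protocol article*

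**What the plan says.** The design is non-inferiority on quadriceps thickness, measured by ultrasound before surgery and 3 days after it (Study design; Primary outcome).

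Under Sample size estimation, the inputs are: "Quadriceps thickness is 3.1 ± 0.5 cm in the non-tourniquet group and 3.1 ± 0.6 cm in the tourniquet group". The margin "is 0.31, which is 10% of the average quadriceps thickness in the non-tourniquet group". Alpha is 0.025 one-sided and beta is 0.2. The conclusion is: "We determine that a total of 51 participants per group would have an 80% statistical power". That makes 102 participants, and the section closes: "Estimating that 30% of participants would drop out, a sample size of 130 participants is considered to be adequate for this study".

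Under Statistical analysis, the paragraph on the primary comparison plans a Mann-Whitney U test and adds: "Bonferroni correction is used to reduce the significance level". It gives neither the number of comparisons nor the reduced level. The paragraph before it says: "The missing data of quadriceps thickness and stiffness is imputed by the multiple imputation method". It then gives the imputed results the role of a sensitivity analysis. The Abstract and the outcome sections name thickness as the only primary outcome and list stiffness as secondary.

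**The concern.** There are two mismatches.

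1. **Dropout.** A target of 102 evaluable with 30% loss is not met by enrolling 130. The protocol uses both the loss rate and the power to justify its size, and the Abstract describes the sample as sufficient on that footing.
2. **Significance level.** The calculation spends the whole one-sided 0.025 on one outcome. The analysis section says that the level for the primary comparison will be reduced. A reduction implies more than one test, but only one primary outcome is named.

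In a non-inferiority trial, lost power means a greater chance of an inconclusive result when the tourniquet is in truth no worse. An unstated divisor also leaves the primary significance threshold open until someone chooses it.

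**Working it through.** **Inputs (Sample size estimation):** margin 0.31 cm; SD 0.5 (non-tourniquet) and 0.6 (tourniquet); true difference 3.1 − 3.1 = 0; one-sided alpha 0.025; target power 80%; 30% dropout; 130 enrolled. Allocation is 1:1 (Allocation and randomization).

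**Step 1. Reproduce the 51 per group.**
- Average SD = √[(0.5² + 0.6²)/2] = √0.305 = 0.552.
- Normal approximation: n = 2 × [0.552 × (1.960 + 0.842)/0.31]² = 49.8, so 50 per group.
- Noncentral t: SE = √(0.25/51 + 0.36/51) = 0.1094; noncentrality = 0.31/0.1094 = 2.83; power = 80.1%. At 50 per group power is 79.3%, so 51 is the smallest adequate number.

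The plan's 51 is therefore correct, and the fault lies after this step.

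**Step 2. The dropout allowance.**
- Evaluable at 30% loss: 130 × 0.70 = 91, which is 102 − 91 = 11 short.
- Enrolment needed: 102/(1 − 0.30) = 145.7, so 146 (73 per group), 16 more than 130.
- The common shortcut of multiplying instead of dividing, 102 × 1.3 = 132.6, does not give 130 either.
- Largest loss that 130 can absorb: 1 − 102/130 = 21.5%.

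**Step 3. Power at the loss actually assumed.** With 45 and 46 evaluable, SE = 0.116, noncentrality is about 2.68, and power is 75.3% to 75.5% depending on which group has 46. The normal approximation gives 76.3%.

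**Step 4. Power at 130 enrolled over a range of loss (t-test basis, one-sided 0.025).** The rates of 0, 5, 10, 20 and 25% are illustrative; 21.5% comes from step 2 and 30% is the plan's figure.

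| Loss | Evaluable per group (average) | Power |
|---|---|---|
| 0% | 65 | 89% |
| 5% | 61.75 | 87% |
| 10% | 58.5 | 85% |
| 20% | 52 | 81% |
| 21.5% | 51 | 80% |
| 25% | 48.75 | 78% |
| 30% | 45.5 | 75% |

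**Step 5. Bonferroni.** The document gives no divisor. With a divisor of 1 nothing changes. As an illustration only, an assumed divisor of 2 makes the level 0.025/2 = 0.0125 one-sided. Power is then 71.1% at 51 per group and 65.3% to 65.5% at 45/46, and 80% would need 62 per group.

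**Step 6. The planned test.** Steps 1 to 5 rest on a comparison of means, while the plan tests with Mann-Whitney U. Assuming normal data and a relative efficiency of 0.955, 51 per group act like 51 × 0.955 = 48.7 (power about 78%), and 45.5 per group like 45.5 × 0.955 = 43.5 (about 73%), both at one-sided 0.025. The plan says that the outcome is not Gaussian, so these two figures only indicate the order of the difference.

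**The case against.** The strongest reply is that the 30% is not tied to any visit. Follow-up runs to 1 year, whereas the primary outcome is measured on day 3, when few participants may yet be lost. At 10% loss or less, 130 enrolled gives 85% power or more. This stands, and it rules out the flat claim that the trial lacks 80% power. A reader might infer that claim from the arithmetic, but the documents show only that 30% loss and 80% power are incompatible at 130. The reply does not remove the conflict, because the 30% is the protocol's own allowance in the calculation for the primary outcome. Early losses are also possible: the Intervention section excludes participants who need certain drugs outside the protocol, and gives no rate.

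Multiple imputation does not close the gap, since the plan makes it a sensitivity analysis and not the main comparison.

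On Bonferroni, a reader might infer that the analysis level is known to be lower than the design level, or that stiffness has become a second primary outcome. Neither is supported. No divisor is stated. The same section refers both to primary outcomes in the plural and to the primary endpoint in the singular. Stiffness appears in the paragraph on missing data, not in the one on the primary comparison, and imputing a secondary outcome does not make it primary. What remains is an inconsistency: either the Bonferroni sentence has no purpose for a single primary outcome, or the sample size calculation omitted it.

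**Conclusion.** The point holds in conditional form. The 51 per group is right and the dropout allowance is wrong. At the plan's own 30% loss, power is about 75% instead of 80%, a shortfall of about 5 percentage points. At 21.5% loss or less, the stated 80% is met. These figures assume a t-test at one-sided 0.025, the plan's SDs and margin, and no true difference.

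The Bonferroni sentence conflicts with a calculation made for one outcome at the full level. Its cost in power cannot be fixed from the document. It is zero for a divisor of 1 and grows with any larger divisor, and the figures for a divisor of 2 are an illustration.

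This should be corrected, but it does not undermine the design: the loss is modest, depends on dropout that may not occur by day 3, and can be dealt with in the text.

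**What to change.** No additional enrolment is asked for.

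1. Replace the closing statement of the sample size section with wording such as: *130 participants give 80% power (two-sample t-test basis) if loss for the day-3 primary outcome is at most 21%; at 30% loss power is about 75%.* Add that the planned Mann-Whitney U test gives slightly less, about 78% and 73% respectively, under normality with an assumed efficiency of 0.955.
2. State in the analysis section that quadriceps thickness is the single primary outcome, tested at one-sided 0.025, and delete the Bonferroni sentence from the primary comparison.

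The cost is a change of text and a slightly less favourable statement of the power or of the tolerated dropout. The change should be made before the analysis so that the primary threshold is fixed in advance.

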### Dissemination plan

The results of the trial will be submitted to an international peer-reviewed journal. The results will also be presented at national and international conferences relevant to the subject fields. Researchers who have a contribution to this study will be listed in the authorship or acknowledgements. The full protocol, participant-level dataset, and statistical code are granted public access.

## Discussion

Tourniquet is now widely used in TKA, but its latent adverse effects are problems that we cannot neglect. Some researchers recommend regular tourniquet application in TKA because of its advantage in reducing intraoperative blood loss and operation time. Other researchers hold an opposite idea. They believe that tourniquet application has obvious damage to quadriceps and extra side effects such as pain, swelling, and blood loss, which may go against patients’ Enhanced Recovery After Surgery (ERAS), so they resist using a tourniquet in TKA. After years of studies including meta-analysis and randomized controlled trials, tourniquet application in TKA is still in dispute.

Tourniquet effects on quadriceps morphology and function are controversial. It is generally considered that tourniquet does have certain damage to the quadriceps, but how bad it can be and what effects it will have on patients are confusing. Leurcharusmee et al. [6] hold the point that tourniquet application can cause ischemia-reperfusion injury to quadriceps, which leads to the release of both oxygen free radicals and inflammatory cytokines. Dennis et al. [23] found in a prospective trial that tourniquet application can reduce quadriceps strength in 3 months after surgery. Guler et al. [24] found that tourniquet use in TKA can decrease the thigh and quadriceps muscle volumes. However, Jawhar et al. [13] reported that tourniquet has no significant effects on quadriceps strength and function. Ayik et al. [25] also reported that avoiding tourniquet cannot improve quadriceps strength after TKA.

It is generally considered that tourniquet application can significantly reduce intraoperative blood loss, but its effects on total blood loss are not explicit. Zhao et al. [15] found out in a randomized controlled trial that tourniquet application may increase hidden blood loss and total blood loss. However, Liu et al. [10] conducted a meta-analysis and found that tourniquet has no significant effects on total blood loss. Herndon et al. [3] hold another idea that tourniquet may reduce total blood loss but has no effects on postoperative blood transfusion rate.

Postoperative pain is an important outcome for TKA patients. It can be evaluated by VAS score as well as opioid consumption. Tourniquet effects on postoperative pain are also controversial. Liu et al. [7] hold the point that tourniquet application can increase postoperative pain, which may be caused by ischemia-reperfusion injury and the release of cytokines. Ajnin et al. [16] and Dong et al. [9] both reported that not using tourniquet in TKA can reduce the patient’s postoperative pain and be beneficial to their recovery. While a randomized controlled trial conducted by McCarthy et al. [4] reported that tourniquet application had no significant effect on thigh pain. Palanne et al. [26] also reported that tourniquet application could not affect pain management and postoperative opioid consumption.

Lower limb swelling is also related to postoperative recovery. It can be measured by thigh circumference. Tourniquet effects are still disputable in respect of swelling. Ajnin et al. [16] and Wang et al. [27] both reported that patients without tourniquet application showed less lower limb swelling. However, Alexandersson et al. [28] reported that tourniquet application had no significant effects on limb swelling.

Postoperative inflammation process is also in association with tourniquet application. It can be reflected by the CRP level in the blood. A randomized controlled trial conducted by Cao [29] reported an increase in inflammatory mediators in tourniquet application such as TNF-α, PTX3, CCL2, PGE-2, and SOD-1, and its degree of elevation is positively correlated with the tourniquet time, which is considered relative to ischemia-reperfusion injury caused by a tourniquet. Zhao et al. [15] also reported that the absence of tourniquet application could reduce the postoperative inflammation process.

Above all, there is still no consensus on tourniquet effects on quadriceps morphology and function, blood loss, postoperative pain, lower limb swelling, and other outcomes for patients undergoing TKA. Tourniquet-related side effects are mainly about quadriceps injuries, so we decide to concentrate ourselves on tourniquet effects on quadriceps morphology and function and design this single-blind randomized controlled trial to offer advice for tourniquet application in clinical practice.

There is now little study about quadriceps morphology of patients after TKA. Quadriceps thickness is selected as the primary outcome to reflect quadriceps morphology, which is measured by an ultrasound test. Innovatively, we use shear wave elastography (SWE) to evaluate quadriceps stiffness. SWE is an evolving ultrasound technique which is progressively used in the musculoskeletal system to evaluate tissue elasticity [30–32]. It is reported to evaluate the stiffness of soft tissues such as quadriceps tendon or medial collateral ligament in healthy people [33, 34], but it has never been used to assess quadriceps stiffness of patients undergoing TKA. Shear waves propagate faster through stiffer tissue so we decide to measure shear wave velocity along the long and short axes of quadriceps to represent quadriceps stiffness [35, 36]. Additionally, we include three tests of rehabilitation department. The isokinetic muscle strength test has been proved to be valid in the assessment of muscle strength in TKA patients [37, 38]. Three-dimensional gait analysis is a useful clinical test to evaluate gait abnormality which can be captured by cameras placed around a walkway [39]. Posture stability testing is also used in our study to monitor the displacement of the plantar pressure center [40]. These 3 tests can provide important indicators to evaluate quadriceps function for TKA patients.

Other outcomes including intraoperative and postoperative blood loss, blood transfusion rate, thigh circumference, VAS score, opioid consumption, d-dimer and C-reactive protein level in the serum, knee function score, postoperative satisfaction score, and complications in the tourniquet group and non-tourniquet group will be evaluated. These outcomes work as effective supplements to our study to further evaluate tourniquet effects on TKA patients.

What’s more, tourniquet time is also a meaningful indicator. As tourniquet is used throughout the whole operation period, it can be represented by operation time. Quadriceps injury and many other side effects may be time-related, so we hope to further investigate the relationship between tourniquet time and tourniquet effects in this study.

Indeed, there are several limitations to our study. First, an ultrasound test is examiner-dependent. Though all the patients are tested by the same ultrasound examiner, it may still affect the validity of the assessment to some degree. Second, tourniquet effects on patients may be too subtle to be reflected by chosen outcomes like VAS score or knee function score. More sensitive outcomes for patients after TKA are needed. Third, this study mainly focuses on clinical outcomes of tourniquet effects. There is a lack of deeper study of the mechanism of ischemia-reperfusion and inflammation.

This study is precisely designed to clarify the effect of tourniquet application on the morphology and function of quadriceps in patients undergoing total knee arthroplasty and offer advice for tourniquet use in clinical practice. Indeed, tourniquet application cannot be determined by one single trial, but we believe that more high-quality studies will be conducted and tourniquet impact will be clarified in the foreseeable future.

